### Genome sequencing

Selected organisms (on the basis of their susceptibility profiles and resistance gene content) will be genome sequenced. We aim to sequence the greatest cross-section of organism groups as possible (ie, all *Staphylococci* or all *Klebsiella*). Selected bacterial isolates will be sequenced at OUCRU in Vietnam. Briefly, index-tagged paired end Illumina sequencing libraries will be prepared using one of 96 unique indexing tags as previously described. These will be combined into pools of uniquely tagged libraries and sequenced on the Illumina Genome Analyzer or HiSeq sequencer according to manufacturer’s protocols to generate tagged 54–100 bp paired-end reads. This is previously approached for describing Gram-negative organisms and *Staphylococcus*.^20 30 31^

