**Method and analysis:**

We will conduct a prospective observational study to characterise the clinical and microbiological features of neonatal sepsis in a major children’s hospital in HCMC. All bacteria isolated from blood subjected to whole genome sequencing. We will compare clinical variables and outcomes between different bacterial species, genome composition and AMR gene content. AMR gene content will be assessed and stratified by species, years and contributing hospital departments. Genome sequences will be analysed to investigate phylogenetic relationships.

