### Study procedures

An investigator will routinely record and collect demographic, clinical and laboratory information of the patients, the date of blood draw, the number of blood culture bottles inoculated, the result of the culture (whether positive or negative) and the susceptibility of the isolate to commonly used antimicrobials. Data from these records will be subsequently entered into CliRes Data Management System of OUCRU. These will be source data for this study. The number of patients admitted to the hospital annually will be obtained from hospital records. As part of this study, we request that all isolates from blood are stored and archived at –80°C. These isolates will be recultured and the identification will be reconfirmed. Selected isolated organisms from blood will have further molecular characterisation at a later date.

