### Microbiological assessments

Available routine microbiology data on neonatal bloodstream infections Children’s Hospital 1. These data will include pathogenic agents isolated from blood culture and antimicrobial susceptibility profile of isolated bacteria (routine panel of antimicrobials). Selected isolates will have additional antimicrobial susceptibility testing, molecular analysis for antimicrobial resistance genes and genome sequencing of selected strains defined by antimicrobial susceptibility data.

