### PCR for resistance genes

The primary focus study is to investigate the distribution of antimicrobial resistance genes in bacteria causing neonatal sepsis. Therefore, all Gram-negative organisms will be investigated by PCR to detect genes catalysing resistance to cephalosporins, fluoroquinolones and carbapenems. Conventional PCR will be performed for the following classes of resistance genes using previously described methods. The multiplex and monoplex PCRs are described in these publications. PCR will be used to detect AmpC, ESBL (including CTX-M15), NDM, qnr, OXA, KPC and mecA/Van.^11 24–29^

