### Antimicrobial resistance genes and genome sequencing

The presence/absence of antimicrobial resistance genes will be reported as proportions per organism and then stratified by organism, year and hospital department. Genome sequences will be determined to study phylogenetic relationships, the presence/absence of virulence genes and also AMR gene content and first analysed by species and then group by their Gram-stain results. Briefly, for phylogenetic analysis, chromosomal single nucleotide polymorphism (SNP) alleles will be concatenated for each strain to generate a multiple alignment of all SNPs. For maximum likelihood (ML) analysis, RAxML will be run using the generalised time-reversible model and 1000 bootstrap pseudoreplicate analyses were performed to assess support for the ML phylogeny. Root-to-tip branches will be extracted from the ML tree using the programme TreeStat. The relationship between root-to-tip distances and year of isolation will be analysed using linear regression. For Bayesian Evolutionary Analysis Sampling Trees (BEAST) analysis (V1.6), a GTR+Γ substitution model and defined tip dates as the date of isolation will be used.^30 31^ To detect the presence or absence of genes read sets will be assembled using the de novo short read assembler Velvet and Velvet Optimizer. Organism specific read sets will then be aligned to the pangenome. Taxonomic investigation of accessory and AMR genes will be performed using MG-RAST V.3.2.

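### The abstract says every blood isolate is sequenced but the methods sequence a subset chosen on resistance, so genome-derived frequencies may not represent the isolates

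*Protocol article*

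**What the plan says.** The protocol article states the coverage of the molecular work in several places, and they differ.

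- **Abstract, Method and analysis:** "All bacteria isolated from blood subjected to whole genome sequencing". It then promises comparisons of outcome by genome composition and resistance gene content, and gene content stratified by species, year and department.
- **Study procedures:** "Selected isolated organisms from blood will have further molecular characterisation at a later date". No basis for the selection is given here.
- **Microbiological assessments:** selected isolates receive "molecular analysis for antimicrobial resistance genes and genome sequencing of selected strains defined by antimicrobial susceptibility data".
- **PCR for resistance genes:** "all Gram-negative organisms will be investigated by PCR to detect genes catalysing resistance to cephalosporins, fluoroquinolones and carbapenems". The listed targets also include mecA/Van.
- **Genome sequencing:** "Selected organisms (on the basis of their susceptibility profiles and resistance gene content) will be genome sequenced". The same section adds "We aim to sequence the greatest cross-section of organism groups as possible", with every Staphylococcus or every Klebsiella as examples, and does not say how this combines with selection on resistance.
- **Antimicrobial resistance genes and genome sequencing:** this section opens with the planned tabulation, "The presence/absence of antimicrobial resistance genes will be reported as proportions per organism and then stratified by organism, year and hospital department". The source, PCR or genome, is not named. The next sentence takes phylogeny, virulence genes and resistance gene content from the genomes, by species and then by Gram stain.

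The Sample size section expects about 400 isolates from 800 participants. No number to be sequenced is given.

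**The concern.** There are two linked problems.

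First, a reader of the abstract would take the genomes as a census of the blood isolates. A reader of the methods would take them as a purposive subset. The sections also disagree on whether resistance-gene testing covers every Gram-negative isolate or only selected ones.

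Second, the stated selection variables are susceptibility and resistance gene content, and resistance gene content is one of the things then described from the genomes. When inclusion depends on the quantity being described, or on something correlated with it, the crude frequency in the subset does not estimate the frequency among all isolates. If selection intensity differs between years or departments, the artefact can look like a trend or a department effect. A tree built mostly from resistant isolates can also show resistant lineages as more prominent than they are.

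This matters because determining the genome sequences is a primary objective, and the department distribution of genes is meant to inform on circulation within the hospital.

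**Working it through.** **Which outputs depend on selection for sequencing**

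| Output | Source if the sections are read together | Depends on selection? |
|---|---|---|
| PCR-panel genes (cephalosporin, fluoroquinolone, carbapenem resistance) in Gram-negatives | PCR of every Gram-negative | No, if the PCR section is followed; yes, if Microbiological assessments is followed |
| mecA/Van in Gram-positives | On the PCR list, coverage not stated | Unclear |
| Virulence genes, resistance genes off the panel | Genome only | Yes |
| Phylogeny, comparisons by genome composition | Genome only | Yes |

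Selecting on resistance gene content requires that content to be known beforehand. This fits PCR of all Gram-negatives as a first step and supports following the PCR section.

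**Figures in the document.** The only relevant ones are 800 participants and about 400 isolates (400/800 = 50%). Nothing fixes a sequencing fraction, so everything below rests on assumed inputs.

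**Case A: carriage itself drives selection.** Let p be the true share of isolates carrying a gene and r the sequencing fraction in carriers divided by that in non-carriers. Then

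observed share = p·r / (p·r + 1 − p).

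For p = 0.30:
- r = 1: 0.30/1.00 = 30%
- r = 2: 0.60/(0.60 + 0.70) = 46%
- r = 4: 1.20/(1.20 + 0.70) = 63%
- r = 8: 2.40/(2.40 + 0.70) = 77%

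Over the same r = 2, 4 and 8, a true 10% is seen as 18%, 31% and 47%, and a true 50% as 67%, 80% and 89%.

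**Case B: the gene is only partly tied to the selecting phenotype.** This is nearer to a virulence gene or an off-panel resistance gene. Assume 40% of isolates are resistant, with the gene in 60% of resistant and 5% of susceptible isolates. The true share is 0.4 × 0.60 + 0.6 × 0.05 = 27%. With resistant isolates sequenced r times as often, their share of the genomes is w = 0.4r/(0.4r + 0.6), and the observed share is 0.60w + 0.05(1 − w):
- r = 2: w = 0.571, observed 36%
- r = 4: w = 0.727, observed 45%
- r = 8: w = 0.842, observed 51%

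A gene equally common in resistant and susceptible isolates would show no bias.

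**Strata.** With the same true 30% in two departments, but r = 1 in one and r = 4 in the other, Case A gives 30% against 63%.

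**Does weighting repair it?** Take 400 isolates under Case B: 160 resistant sequenced at 80% (128 genomes) and 240 susceptible sequenced at 20% (48 genomes).
- Crude: (128 × 0.60 + 48 × 0.05)/176 = 79.2/176 = 45%
- Weighted: (76.8/0.8 + 2.4/0.2)/400 = (96 + 12)/400 = 27%, the true value

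Sequencing every isolate (r = 1) also removes the bias.

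**The case against.** The other side has several good points.

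- **PCR.** A reader might infer that all the gene proportions by organism, year and department will be wrong. The document does not support that. Every Gram-negative is to have PCR for the three drug classes, and the sentence promising stratified proportions does not mention sequencing. Those proportions, and most of what the two secondary objectives ask for, need not rest on genomes. This stands, subject to the conflict with Microbiological assessments.
- **MRSA.** One might infer that the hypothesis about methicillin-resistant S. aureus depends on sequencing. It does not: mecA is on the PCR list and Microbiology testing includes oxacillin for Gram-positives. What remains is that the only coverage statement for PCR names Gram-negatives.
- **Outcome associations.** One might infer that all associations between genes and outcome are distorted. Selection is on exposure, not on death, stay or cost, and sampling on an exposure alone does not bias the outcome risk given that exposure. This stands. There could be distortion for genes imperfectly tied to the selecting phenotype, but its size is not established here.
- **Direction and size.** Nothing says resistant isolates are sampled more often, and sequencing whole organism groups leaves proportions within a group unbiased. This also stands, so the percentages above only illustrate.
- **Condensed article.** Sampling fractions and weights may well be in a fuller document, and their absence is not the point. The point is that the article states coverage in incompatible ways and names resistance as the basis of selection.

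**Conclusion.** The contradiction is plain in the text: all isolates in the abstract, a selection in the methods, plus a second conflict over who receives resistance-gene testing. Under the selective rule, genome-derived frequencies, phylogeny and descriptions by genome composition may not represent the blood isolates. For the PCR-panel genes in Gram-negatives the concern falls away if the PCR section is followed.

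The size is unknown. It depends on how strongly selection follows resistance and how closely a gene is tied to it. A true 30% seen as 46% to 77% assumes that carriage itself drives selection at ratios of 2 to 8. Under the looser tie assumed in Case B, a true 27% is seen as 36% to 51%. At a ratio of 1 there is no bias.

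**What to change.** 1. Reconcile the abstract, Study procedures, Microbiological assessments, PCR for resistance genes and Genome sequencing, so that each gives the same coverage for PCR and for sequencing.
2. Base the resistance gene proportions by organism, year and department on PCR of all isolates, with the source and denominator named. State that the mecA/Van PCR applies to all relevant Gram-positives.
3. For genome-derived frequencies, adopt one of these: sequence all isolates, as the abstract says; choose the subset without regard to resistance; or record the sampling fractions and weight by their inverse.
4. If none of these is adopted, label the genome results as describing the sequenced subset only, and make no prevalence, trend or department claim from them.

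**Cost.** Reconciling and labelling need only wording. Weighting adds a record of how each genome was chosen and a little analysis work. Choosing without regard to resistance may leave fewer resistant genomes for description. Sequencing all of the roughly 400 expected isolates adds laboratory cost that the document does not allow one to estimate, but all isolates are to be stored at –80°C, so the material should be available. The main downside of the cheapest route is narrower genome-based claims.

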## Analysis plan

### Statistical comparisons

Data will be presented in the form of tables and bar charts for descriptive variables, that is, number of organisms per year and number of AMR organisms per year. Statistical comparisons of features between groups (positive/negative blood culture, Gram-negative/Gram-positive bacteria, survival/non-survival, etc) and time trend analysis of the cultured isolates by month and the antimicrobial susceptibility patterns will be conducted. These data will be placed in the context of the broader population by comparison of these data with historical laboratory records of pathogens isolated from patients with bloodstream infections. Historical data from both neonates and older children will be analysed descriptively, and where appropriate, time trend analyses will be performed to determine significant alterations in bloodstream infection aetiology. All statistical analysis will be performed using Stata V.14 and R. P values of ≤0.05 will be considered significant.

### Antimicrobial resistance genes and genome sequencing

The presence/absence of antimicrobial resistance genes will be reported as proportions per organism and then stratified by organism, year and hospital department. Genome sequences will be determined to study phylogenetic relationships, the presence/absence of virulence genes and also AMR gene content and first analysed by species and then group by their Gram-stain results. Briefly, for phylogenetic analysis, chromosomal single nucleotide polymorphism (SNP) alleles will be concatenated for each strain to generate a multiple alignment of all SNPs. For maximum likelihood (ML) analysis, RAxML will be run using the generalised time-reversible model and 1000 bootstrap pseudoreplicate analyses were performed to assess support for the ML phylogeny. Root-to-tip branches will be extracted from the ML tree using the programme TreeStat. The relationship between root-to-tip distances and year of isolation will be analysed using linear regression. For Bayesian Evolutionary Analysis Sampling Trees (BEAST) analysis (V1.6), a GTR+Γ substitution model and defined tip dates as the date of isolation will be used.^30 31^ To detect the presence or absence of genes read sets will be assembled using the de novo short read assembler Velvet and Velvet Optimizer. Organism specific read sets will then be aligned to the pangenome. Taxonomic investigation of accessory and AMR genes will be performed using MG-RAST V.3.2.

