### Secondary objectives

To determine the AMR profiles and gene distribution of isolated bacteria by clinical departments to add insight into the circulation of bacteria associated with hospital acquired infections.To study the genes catalysing resistance to antimicrobials commonly used to treat neonatal sepsis (specifically third/fourth generation cephalosporins, fluoroquinolones and carbapenems).

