## Sample size

In this prospective observational study, we aim to recruit all patients with available data who fulfil the inclusion criteria and are admitted to Children’s Hospital 1 in Ho Chi Minh City in Vietnam from 2017 to 2019. Based on retrospective surveillance data, we estimate recruitment of 800 participants during the study period. Blood cultures will be performed in all cases, we expect to yield ~400 bacterial isolates.

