### Duration and current status of study

The first patient was recruited in January 2017. At the current time, the recruitment is ongoing. The expected end date for recruitment is 31 December 2019. We expect to have completed our data analysis plan with a view of results by June 2020.

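### A p-value or interval from the root-to-tip regression would be too optimistic if isolates of one clone are also sampled close together in time

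*Protocol article*

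**What the plan says.** The analysis plan, under Antimicrobial resistance genes and genome sequencing, builds a maximum likelihood tree from concatenated SNPs. It then states: "Root-to-tip branches will be extracted from the ML tree using the programme TreeStat". The next step is: "The relationship between root-to-tip distances and year of isolation will be analysed using linear regression". A tip-dated BEAST analysis follows, in which "a GTR+Γ substitution model and defined tip dates as the date of isolation will be used".

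Under Statistical comparisons, directly after naming the software for all statistical analysis, the article sets the criterion: "P values of ≤0.05 will be considered significant". Sidedness is not stated.

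On the data, the Sample size section says "we expect to yield ~400 bacterial isolates" over all species, with no number per species or per tree. The status section gives the window: "The first patient was recruited in January 2017" and "The expected end date for recruitment is 31 December 2019". For study isolates, year of isolation therefore takes three values: 2017, 2018 and 2019.

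**The concern.** A root-to-tip distance is a sum of branch lengths, and two isolates of one clone share nearly all of those branches. A clone of ten therefore supplies little more than one independent distance, entered ten times. This does no harm to the p-value if the ten isolates are scattered over the study period. If they were collected within a short spell, as in a ward outbreak, clone identity determines both the distance and the date. A handful of clones that differ in depth and in timing can then give a small p-value although divergence does not increase with time.

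The weakness lies in the unit of analysis. Exact dates in place of calendar years, or an alignment free of recombination, would not remove it.

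At stake is how far evolutionary rates and dates can be trusted. A tip-dated BEAST run returns a rate and dates whether or not the data carry temporal signal, and this regression is the only analysis described that bears on that signal.

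**Working it through.** **Inputs from the document.** Ordinary linear regression on tips of one tree; year of isolation as regressor; P ≤0.05 (taken as two-sided); about 400 isolates over all species; three calendar years. The document gives no error rate for this regression, so there is no stated figure to reproduce.

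**Assumptions.** Number and size of clones, similarity within a clone, and clustering in time. None is in the document, so ranges are shown.

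**Step 1: approximate size.** With m isolates per clone, the variance of the slope is understated by about

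D = 1 + (m − 1) × ICC(distance) × ICC(time),

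and the true two-sided error at nominal 5% is about 2 × [1 − Φ(1.96/√D)].

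Take 100 isolates in 10 clones, so m = 10. Let q be the probability that an isolate falls in its clone's own year; then ICC(time) is about q².

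| q | ICC(distance) | D | Formula | Simulated | Of which positive slope |
|---|---|---|---|---|---|
| 0 | 0.9 | 1 + 9×0.9×0 = 1.0 | 0.050 | 0.049 | 0.025 |
| 0.5 | 0.5 | 1 + 9×0.5×0.25 = 2.1 | 0.18 | 0.171 | 0.087 |
| 0.5 | 0.9 | 1 + 9×0.9×0.25 = 3.0 | 0.26 | 0.274 | 0.138 |
| 1 | 0.5 | 1 + 9×0.5×1 = 5.5 | 0.40 | 0.428 | 0.217 |
| 1 | 0.9 | 1 + 9×0.9×1 = 9.1 | 0.52 | 0.574 | 0.291 |

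The formula uses a normal approximation and runs a little low when clones are few and strongly clustered.

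**Step 2: wider grid, calendar year as regressor.** 40, 100 or 200 isolates in 5, 10 or 20 clones; 2000 datasets per cell; no true clock. Two-sided false-positive rates:
- independent isolates: 0.043;
- clones spread at random over the years (q = 0): 0.043-0.059;
- partial clustering (q = 0.5): 0.063-0.564;
- each clone confined to one year (q = 1): 0.108-0.797, with positive slopes in 0.052-0.401.

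Regression on clone means gives 0.035-0.059 in every cell.

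**Step 3: mixtures of clones and unrelated isolates, continuous dates.** Poisson 100 SNPs shared per clone, Poisson 2 private SNPs, clone dates uniform over 3 years, within-clone SD 0.2 year, 4000 datasets each. Repeated runs agree to within simulation error:

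| Structure | Two-sided |
|---|---|
| 6 clones of 10 | 61-63% |
| 6 clones of 10 + 20 singletons | 49-50% |
| 6 clones of 5 + 30 singletons | about 25% |
| 10 clones of 4 + 20 singletons | 26-27% |
| All singletons | 5% |

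Counting only positive, clock-like slopes, the four clonal structures give about 12-32% against a nominal 2.5%. Clone-level regression gives 4.6-5.6%. Clones spread evenly over the window give 5.3%.

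These settings are strong: ICC(distance) = 100/(100 + 2) = 0.98, and ICC(time) = 0.75/(0.75 + 0.04) = 0.95, where 0.75 = 3²/12 and 0.04 = 0.2².

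**Step 4: trees in place of discrete clones.** On random coalescent trees whose sampling years follow the tree, the two-sided rate is 0.54 (30 tips) and 0.75 (100 tips), of which 0.27 and 0.39 are positive. With years shuffled over tips it is 0.052 and 0.049. The inflation therefore comes from dates clustering on the tree. Shared ancestry alone does not cause it.

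**The case against.** **The regression is not called a test.** The article says that the relationship is analysed. It states no hypothesis of temporal signal and no rule that BEAST goes ahead if P ≤0.05. The significance criterion stands in another subsection and reaches this regression only through the general words on all statistical analysis. A reader might infer that the plan uses the regression as a pass/fail gate for dating; the text does not say so. This stands, and it makes the point conditional on a p-value or interval being used.

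**No harm to a stated objective is shown.** A reader might infer that wrong dates for the emergence or persistence of hospital clones will follow. No objective mentions such dates. The secondary objective that aims "to add insight into the circulation of bacteria associated with hospital acquired infections" relies on resistance profiles and gene distribution by department, with no molecular clock. This stands too.

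**The clone structure is assumed.** Community-acquired cases, referrals from several provinces, the exclusion of previously recruited patients and the wish to sequence a broad cross-section all point to some diversity. With clones spread over the window the regression holds its level, so it would be wrong to say that it is valid only for unrelated isolates. The high figures describe strong clustering and do not forecast this study. A negative slope would not be read as a clock, so the positive-slope rates are the relevant ones.

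**The article is condensed.** It introduces the phylogenetic methods as a brief account and cites sources for them. That it does not mention date randomisation or a clock model is therefore no fault.

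What remains is the method the article does name: least squares on related tips, under a general significance rule, next to a tip-dated analysis.

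**Conclusion.** The point holds in a limited, conditional form. If a p-value or confidence interval from this regression is reported or relied on, it overstates the evidence whenever clone-mates are close both in distance and in time. Single-hospital recruitment, with an interest in hospital circulation, makes this plausible; nothing in the document establishes it.

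For the four mixed structures examined, the false clock-like rate is about 12-32% against 2.5%. Over the wider grid it runs from nominal, with no clustering in time, to about 40% with 200 isolates in 5 clones each confined to one year. All these rates rest on assumed clone numbers, sizes and clustering.

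Only rate and dating statements from the genomic analysis are affected. The clinical, aetiology and susceptibility results are not.

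**What to change.** State that the root-to-tip plot and slope are descriptive and carry no p-value. Add that, if temporal signal is claimed or BEAST rates and dates are reported for a species or lineage, the signal is first assessed in one of two ways:
- a regression with one point per clone; or
- a date-randomisation test that groups tips into monophyletic clones sampled close in time and permutes dates between clones.

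Permuting dates between single isolates is not enough, because it destroys the clustering that causes the problem. Report "no temporal signal" in those words, or equivalent, for lineages that do not pass, and give no dates for them.

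The cost is one or two sentences and some computing time; no new data are needed. The drawback is that fewer lineages will qualify. With three clones, for example, there are only 3! = 6 arrangements of the dates, so the smallest attainable one-sided P is 1/6 = 0.17.
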